## Abstract

**Background:**

Tai Chi is a moderately intense exercise that dates back to ancient China. It has been reported that Tai Chi not only has beneficial effects on metabolic disorders, such as diabetes, cardiovascular diseases and obesity, but also has favorable effects on psychological well-being. Since these conditions are quite closely associated with polycystic ovary syndrome (PCOS), we hypothesis that Tai Chi could be a potential treatment option for PCOS patients. We aim to determine the feasibility and effectiveness of Tai Chi on overweight/obese adolescent and young women with PCOS.

**Methods:**

A total of 50 patients will be randomized into two arms: (1) Tai Chi or (2) self-monitored exercise. Both groups will exercise for 3 months. The primary hypothesis is that Tai Chi results in a significantly lower Body Mass Index (BMI) than self-monitored exercise. The study was approved by the Ethics Committee of the First Affiliated Hospital of Heilongjiang University of Chinese Medicine.

**Discussion:**

This is the first study to determine the feasibility and effectiveness of Tai Chi in treating overweight/obese adolescent and young women with PCOS. The trial will provide evidence to assess the feasibility of a future multicenter, randomized controlled trial.

**Trial registration:**

ClinicalTrials.gov, ID: NCT02608554. Registered on 17 November 2015.

**Electronic supplementary material:**

The online version of this article (10.1186/s13063-018-2893-z) contains supplementary material, which is available to authorized users.

## Background

Polycystic ovary syndrome (PCOS) is the most common endocrine disorder and affects 5–20% of reproductive-age women [1]. It is a complex syndrome characterized by reproductive and metabolic implications including amenorrhea /oligomenorrhea, hyperandrogenism (including hirsutism) or acne and very often by overweight and obesity [2, 3].

Overweight or obesity in adults has been defined by the World Health Organization (WHO) (Body Mass Index (BMI) ≥ 25 kg/m^2^ for overweight, BMI ≥ 30 kg/m^2^ for obesity). In studies on Asian subjects, overweight is considered to be a BMI ≥ 23 kg/m^2^and obesity a BMI ≥ 25 kg/m^2^ [4]. For adolescents, age- and gender-specific percentile distributions for BMI using the Centers for Disease Control and Prevention growth charts were used to identify those who were overweight (85th–95th percentile) or obese (> 95th percentile) [5].

The prevalence of overweight and obesity in women with PCOS is highly variable since it differs in the general population according to age, ethnicity and geographic regions. A meta-analysis reported that the prevalence of obesity (BMI ≥ 30 kg/m^2^) in women with PCOS ranged from 12.5 to 100% with a pooled estimated prevalence of 49% (95% CI 42–55%); the prevalence of overweight (BMI ≥ 25 kg/m^2^) and obesity (BMI ≥ 30 kg/m^2^) ranged from 6 to 100% with a pooled estimated prevalence of 61% (95% CI 54–68%). Also, the prevalence of central obesity was significantly higher in women with PCOS compared with controls [6].

Despite the highly variable reported prevalence of overweight and obesity in women with PCOS, it is confirmed that being obese is significantly associated with worse metabolic and reproductive outcomes measured, except for hirsutism, when compared to normal-weight women with PCOS [6]; whereas women who were overweight but not obese only had no differences in total testosterone (T), hirsutism, total cholesterol and low-density lipoprotein cholesterol (LDL-C) compared to normal-weight women, and no differences in sex-hormone-binding globulin (SHBG), total T and fasting lipids compared to obese women [6]. Central obesity was associated with higher fasting insulin [6]. Also, overweight and obesity is associated with unfavorable in vitro fertilization (IVF)/ intracytoplasmic sperm injection (ICSI) outcomes in PCOS patients treated with a gonadotropin-releasing hormone (GnRH) agonist using the long protocol [7, 8].

Therefore, it is of great importance to be aware that overweight and obese PCOS patients, especially adolescent and young women with PCOS, should also be advised to lose weight. This will not only assist with their immediate symptoms but also will help to prevent the development of diabetes and cardiovascular disease in later life. Lean women with PCOS should be cautioned of the high risk of overweight, obesity and central obesity associated with PCOS, and be encouraged to engage in health behaviors that prevent weight gain.

It is confirmed that even modest weight loss of just 5% body weight in obese women with PCOS can restore regular menstruation and improve response to ovulation induction and fertility treatment [9]. Lifestyle modification, use of metformin, taking hormonal contraceptives (HCs), and bariatric surgery are the main treatment options in obese patients with PCOS recommend by guidelines [10]. Lifestyle modification is the first-line management which could both prevent weight gain and induce weight loss. However, improved engagement and sustainability remain challenges while using. Medications such as metformin, HCs and bariatric surgery have been used with the need for large-scale randomized clinical trials to define their roles and side effects. Novel therapies including inositols [11] and statins [12] have been under investigation lately. Complementary and alternative medicine approaches such as Chinese medicine formulas [13] and acupuncture [14] are also under study. Their efficacy and safety still need to be addressed. More research is needed to assign better therapeutic regimens in overweight and obese PCOS patients and strategies to prevent the development of comorbidities.

Tai Chi is an exercise system followed Chinese Medicine theory which dates back to seventeenth century. It can maintain the harmony between *qi* and the blood, keep *yin* and *yang* in balance and has traditionally been used in various forms for the promotion and maintenance of health and longevity in China [15]. Recently, physiological and psychosocial benefits of Tai Chi on chronic diseases which are very closely related to PCOS, such as obesity, cardiovascular diseases (CVD) and type-2 diabetes [16–18], have been addressed.

A recently published randomized controlled trial of 374 Chinese adults reported that, a 12-week Tai Chi training led to significant loss of 0.50 of body weight and 0.47 of fat mass compared with a control group, which is a similar effect as in a walking group [19]. Another randomized clinical trial consisting of 266 Chinese adults with hypertension reported that a 12-month Tai Chi training could significantly lower BMI compared with a control group (22.25 ± 2.91 vs 23.16 ± 2.94, *p* < 0.001) [16].

To the best of our knowledge, there is no study so far investigating the effect of Tai Chi in women with PCOS. Therefore, the purpose of the present study is to evaluate the effect of Tai Chi in PCOS and the feasibility of executing a large-scale clinical trial.

## Methods

### Study design

This present study is a single-blind (assessor), parallel, randomized, pilot feasibility study, which will be carried out to compare Tai Chi with self-monitored exercise in treating PCOS patients. Subjects will be randomly assigned to a Tai Chi group and a self-monitored exercise group with an allocation ratio of 3:2. The study period is 3 months. A flowchart of the study is depicted in Fig. 1. The schedule of trial enrollment, interventions and assessments is provided in Fig. 2 (Additional file 1). This protocol was written following the Standard Protocol Items: Recommendations for Interventional Trials (SPIRIT) Checklist (see Additional file 1).

**Fig. 1 Fig1:**
[figure not shown]
Study design flowchart

**Fig. 2 Fig2:**
[figure not shown]
Schedule of enrollment, interventions and assessments (Additional file 1). Safety eligibility includes liver function, renal function and complete blood count (CBC). t1, 1 month after allocation; t2, 2 months after allocation; t3, 3 months after allocation, t4, the beginning of the 4th month after allocation

### Study setting

The present study is conducted in the First Affiliated Hospital, Heilongjiang University of Chinese Medicine. All study visits and Tai Chi interventions will take place at the above mentioned hospital. Self-monitored exercise will be held in a home-based environment.

### Inclusion criteria

Women aged between 18 and 35 years [19]Confirmed diagnosis of PCOS according to the modified Rotterdam criteria and all subjects must have anovulation plus either polycystic ovaries and/or hyperandrogenism2 years after menarcheBMI equal to or greater than 23 kg/m^2^ [4]With no desire to have children within 6 months

PCOS is defined by the modified Rotterdam criteria as: oligomenorrhea or amenorrhea, together with presence of ≥ 12 antral follicles (≤ 9 mm) and/or ovarian volume > 10 mL on transvaginal scanning, and/or clinical/biochemical hyperandrogenism. Oligomenorrhea is defined as an intermenstrual interval > 35 days and less than eight menstrual bleeds in the past year. Amenorrhea is defined as an intermenstrual interval > 90 days. Clinical hyperandrogenism in mainland China is defined with a Ferriman-Gallwey (FG) score ≥ 5 [20].

### Exclusion criteria

Administration of other medications known to affect reproductive function or metabolism within the past 3 months, including oral contraceptives, gonadotropin-releasing hormone (GnRH) agonists and antagonists, anti-androgens, gonadotropins, anti-obesity drugs, Chinese herbal medicines, anti-diabetic drugs such as metformin and thiazolidinediones, somatostatin, diazoxide and calcium-channel blockersPatients with other endocrine disorder including 21-hydroxylase deficiency, hyperprolactinemia, uncorrected thyroid disease, suspected Cushing’s syndromePatients with known severe organ dysfunction or mental illness

### Interventions

#### Tai Chi

Subjects in the Tai Chi group will practice in the gymnasium of Heilongjiang University of Chinese Medicine. The program of Tai Chi training consisted of a 60-min exercise session, three times per week for 12 weeks, based on their original level of physical activity. Each session comprised 40 min of Tai Chi training plus a 10-min warm-up and cool-down. Tai Chi training was instructed by the same experienced Tai Chi instructors who were qualified in teaching. The 24 forms of simplified Tai Chi recommended as a popular health-benefitting sport by the General Administration of Sport of China was applied. Practice attendance will be monitored and adherence to practice will be recorded.

#### Self-monitored exercise

The subjects of the self-monitored exercise group will be asked to conduct extra exercise besides their routine exercise. The self-monitored exercise consists of brisk walking, cycling, jogging, or any other aerobic exercise for 60 min, three times per week for 12 weeks [21]. Adherence to exercise will be tracked via self-report logs, which will be obtained at the weekly frequency during exercise.

## Outcome measurements

### Primary outcome

The primary outcome measurement is the BMI change from baseline. BMI will be calculated using weight (kg)/height (m^2^).

### Secondary outcomes

Oral glucose tolerance test (OGTT): serum for glucose and insulin levels will be determinedHormonal profile including: testosterone (T), androstadiendione (AND), SHBG, dehydroepiandrosterone sulfate (DHEAS), follicle-stimulating hormone (FSH), luteinizing hormone(LH),and estradiol (E2)Fasting-lipid metabolic profile: cholesterol, triglycerides (TG), cholesterol (CHOL), high-density lipoprotein cholesterol (HDL-C) and low-density lipoprotein cholesterol (LDL-C)Weight, waist/hip circumference, blood pressure, FG score and presence of acne before and after treatmentFeasibility outcomes including participant recruitment rates, retention rates, treatment fidelity monitored through attendance recordsAdverse events

### Sample size calculation

This study is an exploratory study of the evaluation of the effectiveness of Tai Chi for PCOS subjects and the feasibility of a large clinical trial; therefore, the minimum sample size necessary to evaluate the effectiveness was used [22].

For such a trial designed with 90% power and two-sided 5% significance,

the sample size was set to 50 patients with an allocation ratio of 3:2.

### Randomization and allocation concealment

After the baseline evaluation, 50 subjects will be allocated randomly into one of the two groups in a ratio of 3:2. The identification code and random number, which are unique for each subject, were generated using SAS 9.2 by an independent agency (TCM Translational Medicine Research Centre, First Affiliated Hospital, Heilongjiang University of Chinese Medicine). These assignments were put into sealed, opaque envelopes. The envelopes will only be opened after the subject has completed baseline clinical assessments.

### Blinding

The present trial is a single-blinded trial. Outcome assessors and people responsible for the statistical analysis will be blinded to the randomization status.

### Data collection and management

Study-related information, such as participant’s identity, the data collected relating to the study, and medical records, will remain confidential. Case report forms (CRFs) will be completed on paper forms. Data will then be entered and stored in a password-protected electronic database. Original paper copies of CRFs and all study data will be stored in a locker with access allowed to the involved researchers only.

### Data analysis

The intention-to-treat (ITT) principle will be used in the statistical analysis. All participants randomized were involved in the ITT analysis. Data will be summarized using means (± SDs) for continuous variables. An analysis of covariance (ANCOVA) model will be used to compare the mean changes of outcomes from baseline to end of intervention, including baseline measurement as covariates. A paired *T* test or the Wilcoxon rank test will be used to compare variables from baseline to the end of intervention. Data will be presented as frequency for categorical variables. The chi-square test or Fisher’ exact test will be performed to examine differences. *P* < 0.05 will be considered statistically significant. All analysis will be performed using SAS version 9.3.

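### The stated test for categorical outcomes is valid between arms but ignores baseline acne status, which the trial already collects

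*Protocol article*

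**What the plan says.** In the protocol article, the Secondary outcomes section includes whether acne is present, assessed at both ends of treatment. It is the one clearly binary efficacy outcome in that list.

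The Data analysis section treats the two types of data differently:

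- Mean changes are compared between arms by ANCOVA, "including baseline measurement as covariates".
- For change over time, a paired t test or "Wilcoxon rank test will be used to compare variables from baseline to the end of intervention".
- For categorical data: "Data will be presented as frequency for categorical variables". A chi-square or Fisher's "exact test will be performed to examine differences".

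The categorical rule has no baseline term, names no paired test, and does not say which differences it means. Acne is not named there, but the rule covers it as a categorical variable.

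On size, the Sample size calculation section states that "the sample size was set to 50 patients with an allocation ratio of 3:2", which is 30 Tai Chi and 20 self-monitored exercise.

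**The concern.** A woman's acne status at three months is likely to depend on whether she had acne at the start. A chi-square or Fisher test of end-of-intervention acne leaves that variation in the comparison, along with any chance imbalance in baseline acne between groups of 30 and 20. The plan removes the same noise for mean changes but not here, although the baseline value is already on the case report form.

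What is at stake is power and precision for one secondary outcome. The error rate of the between-arm comparison is not in question.

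**Working it through.** **The plan's own figure.** The total of 50 is stated thus: "For such a trial designed with 90% power and two-sided 5% significance". It is not set for acne, and no effect size or SD is given, so it cannot be reproduced. Solving backwards by the normal approximation, 30 versus 20 detects (1.960 + 1.282) × √(1/30 + 1/20) = 3.242 × 0.2887 = 0.94 SD with 90% power. Nothing below depends on this.

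**Inputs.** From the documents: 30 versus 20, two-sided 5%. Assumed, because the documents give none: baseline acne prevalence, persistence (probability of acne afterwards given acne at baseline; Tai Chi versus control) and new acne (probability of acne afterwards given none at baseline).

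**One scenario by hand.** Baseline acne 50%, new acne 10%, persistence 35% versus 85%.

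- Acne afterwards: Tai Chi 0.5 × 0.35 + 0.5 × 0.10 = 22.5%; control 0.5 × 0.85 + 0.5 × 0.10 = 47.5%.
- Chi-square: pooled proportion (6.75 + 9.5)/50 = 0.325. SE = √(0.325 × 0.675 × (1/30 + 1/20)) = 0.135. z = 0.25/0.135 = 1.85. Power ≈ Φ(1.85 − 1.96) ≈ 46%.
- Cochran-Mantel-Haenszel (CMH) at expected counts, 15 versus 10 women per stratum. With n₁ Tai Chi women, n₀ controls, N = n₁ + n₀ and m women with acne afterwards, each stratum contributes observed minus n₁m/N, with variance n₁n₀m(N − m)/(N²(N − 1)).
  - Baseline acne: 5.25 − 15 × 13.75/25 = −3.00; variance 15 × 10 × 13.75 × 11.25/(625 × 24) = 1.547.
  - No baseline acne: 1.5 − 15 × 2.5/25 = 0; variance 15 × 10 × 2.5 × 22.5/(625 × 24) = 0.563.
  - |z| = 3.00/√2.110 = 2.07. Power ≈ Φ(2.07 − 1.96) ≈ 54%.

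**Simulated power (%).** A dash means not run.

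| Baseline acne; new acne; persistence | Chi-square | CMH | Fisher | Exact stratified |
|---|---|---|---|---|
| 50%; 10%; 35% vs 85% | 44 | 56 | 40 | 49 |
| 50%; 10%; 45% vs 85% | 30 | 40 | 26 | 32 |
| 60%; 5%; 35% vs 85% | 59 | 74 | 53 | 68 |
| 50%; 10%; 65% vs 85% | 12 | 14 | 9 | 9 |
| 30%; 10%; 60% vs 85% | 9 | 10 | 7 | 7 |
| 30%; 10%; 35% vs 85% | 23 | 28 | 19 | 21 |
| 30%; 3% vs 5%; 40% vs 90% | 28 | 44 | 24 | – |
| 50%; 15% vs 40%; 25% vs 60% | 61 | 62 | 56 | – |

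Repeat runs of the first three rows moved by about a point, so the gains there are 9–16 points for CMH over chi-square and 6–15 for exact stratified over Fisher. Rows four to six gain 0–5 points. The last two rows show that persistence matters as well as prevalence: the gain is 16 points at 30% baseline acne when acne rarely changes without treatment, and 1 point when baseline acne barely predicts later acne (correlation 0.2).

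**Error rate with no treatment effect.** Chi-square rejected 5.5–5.7% of the time, Fisher 4.3–4.4% and CMH 4.1–5.1%. The exact stratified test rejected 2.6% (baseline acne 50%, new acne 10%, persistence 85% in both arms).

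**The case against.** The strongest reply is that chi-square or Fisher between randomised arms is a correct test, and that adjusting one binary secondary outcome is a preference that could be settled in a fuller plan. The validity part stands. But the article does fix a test for categorical variables, and that test leaves out a covariate of the kind the same section uses for mean changes, so the better choice can fairly be raised.

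Two further replies stand in part. The larger gains need large effects. And sparse strata may force the exact version: in the first and third scenarios the stratum without baseline acne expects only 25 × 0.10 = 2.5 and 20 × 0.05 = 1 women with acne afterwards. The exact version gains less, and in the sixth row it falls below plain chi-square (21% against 23%), though not below Fisher.

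A reader might infer something stronger: that an unpaired chi-square will be applied to before-and-after acne in the same women, and is therefore invalid. The documents do not support this. They never assign chi-square to that comparison, they give baseline-to-end comparisons their own sentence with paired methods, and the two time points in the outcome list describe measurement, not analysis. Nor would such use produce false claims of benefit. With 30 women and a before/after correlation of 0.6, the unpaired test would reject a true null about 0.3% of the time, which is conservative.

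**Conclusion.** The point holds as a minor matter of efficiency. The stated between-arm test is valid but leaves baseline acne unused. Under the assumed large effects with baseline acne of 50–60%, stratification is worth about 9–16 points of power (asymptotic) or 6–15 points (exact, like for like). With smaller effects, or baseline acne near 30% with 10% new acne, it is worth about 0–5 points. All of these figures rest on assumed prevalence, persistence and effect.

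The consequence is limited to one component of the secondary outcomes in a 50-patient pilot. The BMI analysis, the sample size and the feasibility outcomes do not depend on it.

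**What to change.** Add one sentence to the Data analysis section. Acne at the end of the intervention will be compared between arms by a Cochran-Mantel-Haenszel test stratified by baseline acne (exact version if strata are sparse), or by a penalised logistic model with baseline acne as covariate, and the adjusted effect will be given with its 95% CI. Fix the choice, and the rule for switching to the exact version, before unblinding.

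Keep chi-square or Fisher for categorical data with no baseline value, such as adverse events. If acne is tested before and after within an arm at all, name McNemar's test.

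No new data or patients are needed. The cost is that the exact version is conservative in sparse strata and can fall slightly below plain chi-square.

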### Ethics and dissemination

The present study is registered at ClinicalTrials.gov (NCT02608554), and conducted in accordance with the Declaration of Helsinki. The study received approval from the First Affiliated Hospital of Heilongjiang University of Chinese Medicine Institutional Review Boards (approval number HZYLLKT201500201). The result of the present study will be published in a peer-reviewed journal.

### Safety

All adverse events reported during the study period will be documented in the CRF.

Serious adverse events (SAEs) will be notified to the principle investigator and within 24 h. All SAEs must be reported on the Adverse Event page of the CRF. The principal investigator is responsible for the management of the safety reporting according to local guidelines.

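### Adverse events are pooled however they come to light although contact differs by design between the arms, so any between-arm comparison is at risk of unequal ascertainment (low severity, cheap to improve)

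*Protocol article*

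**What the plan says.** In the protocol article, the list under Secondary outcomes ends with adverse events. The Safety section says: "All adverse events reported during the study period will be documented in the CRF". It then sets out how serious events are notified. It does not describe how non-serious events are asked about, or whether the source of a report is noted.

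The two arms have different contact with the trial:

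- **Tai Chi.** The programme is a "60-min exercise session, three times per week for 12 weeks". It is led in person: "Tai Chi training was instructed by the same experienced Tai Chi instructors who were qualified in teaching". Attendance is monitored.
- **Control.** Study setting says: "Self-monitored exercise will be held in a home-based environment". The contact described for this arm alone is the log: "Adherence to exercise will be tracked via self-report logs, which will be obtained at the weekly frequency during exercise".
- **Both arms.** The legend of Fig. 2 defines "t1, 1 month after allocation; t2, 2 months after allocation; t3, 3 months after allocation", and a further point t4 at the start of the fourth month. Study setting places all study visits at the hospital and does not limit them to one arm. The figure showing what is done at each time point is not available.

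Under Blinding, only outcome assessors and analysts are blinded. Data analysis gives chi-square or Fisher's exact tests for categorical data and does not name adverse events.

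**The concern.** An event is counted if it reaches the case report form. If the chance of that depends on how often a participant meets someone connected with the trial, the recorded rate mixes the true rate with contact frequency. A sore knee is easily mentioned to, or seen by, an instructor three times a week. The same complaint after jogging at home has fewer routes into the record.

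The Safety rule combines events volunteered in class with events obtained at visits common to both arms. Tai Chi could then look less well tolerated than home exercise when true rates are equal, or injuries from unsupervised exercise could be missed. The trial is meant to inform a larger multicentre trial, so a distorted safety picture would be carried forward. No later analysis can recover events that were never elicited, or separate the sources if they were not recorded.

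**Working it through.** The article states no adverse event rate or reporting probability, so there is no figure of its own to reproduce. The contact counts follow from the text; every probability below is an assumption.

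**1. Contacts.** Tai Chi: 3 sessions × 12 weeks = 36. Control: 1 log × 12 weeks = 12. Ratio 36/12 = 3. Common to both arms: three contacts (t1 to t3), or four with t4.

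**2. Contact model.** Take a minor complaint that persists throughout and has an independent chance p of being mentioned at each of k contacts. The chance of capture is 1 − (1 − p)^k. Counting a log as equal to a session:

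| Contacts counted (Tai Chi vs control) | p = 5% | p = 10% |
|---|---|---|
| Arm-specific only, 36 vs 12 | 84% vs 46%, ratio 1.83 | 98% vs 72%, ratio 1.36 |
| Plus three common, 39 vs 15 | 86% vs 54%, ratio 1.61 | 98% vs 79%, ratio 1.24 |
| Plus four common, 40 vs 16 | 87% vs 56%, ratio 1.56 | 99% vs 81%, ratio 1.21 |

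Example: 1 − 0.95^36 = 0.842, 1 − 0.95^12 = 0.460, and 0.842/0.460 = 1.83.

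**3. Effective common visits.** Suppose each of three common visits detects the complaint with probability 60%. All three miss it with probability 0.4³ = 0.064. With p = 5% elsewhere, capture is 1 − 0.158 × 0.064 = 0.990 for Tai Chi and 1 − 0.540 × 0.064 = 0.965 for control, a ratio of 1.03. Good elicitation at the common visits nearly removes the problem.

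**4. Effect on a test.** The 3:2 split of 50 gives 30 vs 20. Assume the same true risk in both arms and 90% reporting for Tai Chi. The recorded risk ratio is then 0.9 divided by control reporting. The table gives the exact false-positive rate of a two-sided Fisher test at 5%:

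| True risk | Control reporting 0.9 (ratio 1.00) | 0.7 (1.29) | 0.5 (1.80) | 0.3 (3.00) |
|---|---|---|---|---|
| 10% | 1.5% | 0.9% | 0.7% | 0.9% |
| 20% | 3.3% | 3.6% | 6.1% | 11.5% |
| 30% | 3.6% | 5.6% | 13.0% | 28.8% |
| 50% | 4.2% | 8.9% | 25.7% | 57.2% |

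With equal reporting the ratio is 1.00 and the test stays below 5%. With unequal reporting the estimate is always distorted, but a false significant result becomes likely only when events are frequent and the reporting gap is large.

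**The case against.** The strongest reply is that this is an article, not the full protocol. Its Safety sentence says where reported events are written down. It does not say that reporting is spontaneous or that nothing else is collected, and an event elicited by a question at a visit is also reported. The case report form and the schedule figure, where such questioning would normally appear, are not shown. This stands: it cannot be concluded that active questioning is absent, and a missing description of it is not the point raised here.

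Second, a reader might infer that controls have no contact beyond a log. The text does not support that, since t1 to t4 and the hospital visits are not restricted to one arm. Third, the article does not say that Tai Chi instructors collect or pass on adverse events, so 36 sessions are 36 opportunities at most. Both limit the size, and the second can shrink it almost to nothing.

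Fourth, a between-arm comparison of adverse events is implied by the outcome list and the categorical tests, but not stated, and the trial's main aims are BMI and feasibility. This lowers the importance.

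What survives is that, even with identical questioning at t1 to t4, the rule as written would still pool those answers with whatever is volunteered in class.

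**Conclusion.** The point holds as a risk of unequal ascertainment, not as a demonstrated bias. A reader might go further and say that the comparison is biased or that only spontaneous reports are captured. The article supports neither, because size and direction depend on reporting probabilities it does not give.

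The direction is probably towards a higher apparent rate for Tai Chi, if reporting depends on contact and class events reach the record. The contact calculations give a spurious ratio of about 1.0 to 1.8, resting on an assumed 5% or 10% chance per contact, a persistent complaint, independent contacts and a log counted as equal to a session. The range illustrates and does not bound the effect: capture of 0.9 against 0.3 would give 3.0, but nothing in the article points to so large a gap. The harm is mainly to the estimate. Low severity, and a cheap improvement.

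**What to change.** In the Safety section, state that adverse events are asked about with the same standard question at the same scheduled time points, t1 to t4, in both arms, and that any between-arm comparison uses events elicited this way. Events volunteered in Tai Chi classes or elsewhere are still recorded for safety, with their source marked, and tabulated separately. Reporting of serious adverse events is unchanged. If the schedule already provides for identical questioning, one sentence saying so and the separate tabulation are enough.

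The cost is one question at existing contacts and slightly more minor events recorded in both arms. Recruitment stood at 37 of 50 in January 2018, so a change at that stage would mix two ways of collecting events. For participants already enrolled, events must be tabulated by how they were obtained.
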